#### *Quantitative data analysis*

The quantitative analysis will take place in three parts, each addressing one of the questions of interest. To address the question of whether TeachTown results in reduced use of EBP, we will compare the intervention and control groups in year 1. We will conduct the analysis at the teacher level. We will create three fidelity variables for each of the five EBPs, as we did in aim 2. The analyses will mirror those described in aim 2. To address the question of whether introducing TeachTown affects intentions to use EBPs, we will conduct similar analyses with intentions to use each of the EBPs at time 2 as the outcomes of interest. If intentions are determined to vary as a function of TeachTown use, we then will explore the effects of TeachTown on each of the determinants of intention.

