### Measures

Our primary outcome of interest, in keeping with recent randomized trials of autism interventions, is cognitive gain. Other selected measures are tied to the domains in which TeachTown purports to affect change (see Table 1).

**Table 1 Tab1:** List of measures, respondents, and time points for data collection

Measure	Respondent	Time point
Aim 1: Effectiveness		
Differential Ability Scales, 2nd Edition (DAS-II)	Direct observation of student functioning completed by graduate student or clinician	Beginning and end of year 1
Bracken Basic Concept Scales, 3rd Edition	Direct observation of student functioning completed by graduate student or clinician	Beginning and end of year 1
Autism Diagnostic Observation Schedule—2nd edition (ADOS-2)	Direct observation of student functioning completed by graduate student or clinician	Throughout year 1
Adaptive Behavior Assessment System, 2nd Edition (ABAS-II)	Teacher rating form of child functioning	Beginning and end of year 1
Pervasive Developmental Disorder Behavior Inventory (PDD-BI)	Teacher rating form of child functioning	Beginning and end of year 1
Social Communication Questionnaire (SCQ)	Parent rating form of child functioning	Beginning of year 1
Family Demographic Questionnaire	Parent	Beginning of year 1
Teacher Demographic Questionnaire	Teacher	Beginning of year 1
Aim 2: Implementation		
TeachTown penetration	Computer software logs	Monthly
TeachTown fidelity	Direct observation of teacher behavior conducted by TeachTown staff	Monthly
Intentions and attitudes scale	Teacher rating scale	Mid-year years 1 and 2
Aim 3: Exnovation		
Existing EBP fidelity	Direct observation of teacher behavior conducted by trained research assistants	Monthly

*Cognitive ability* will be assessed using the Differential Ability Scales, 2nd Edition (DAS-II) [41]. The DAS-II assesses cognitive abilities that are important to learning and may be administered to children ages 2 years 6 months through 17 years 11 months across a broad range of developmental levels. A member of the assessment team will administer the DAS-II to students in the study at the beginning and end of the academic year in year 1.

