### Data analyses

Analysis will be based on randomization of classrooms to TeachTown (*n* = 35) or control (*n* = 34). Outcomes will be analyzed at the student level across time. Outcome differences will be estimated with longitudinal nested linear models with random effects for classroom and student [49–51]. All outcome measures are continuous variables.

We also will examine several potential moderators of TeachTown impact, including: (1) symptoms at baseline (measured by the PDDBI); (2) cognitive functioning at baseline (measured by the DAS); (3) penetration (whether the consented student received TeachTown instruction based on the electronic logs); (4) fidelity of program implementation (direct observation of generalization lessons, described in aim 2); (5) use of the EBPs described in Aims 3; and (6) family characteristics, including family composition and parent education and income. Potential moderators will be included in the model as main effects and as interaction terms with time and treatment group factors in the model. The three-way interaction between time, treatment group, and the moderator will be used to assess the presence and magnitude of the moderating effect. Because both TeachTown and EBP fidelity may vary over the course of the year for each student, we will use growth mixture models to categorize fidelity trajectories at the student level.

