### Independent variables

#### *Measures of intention and determinants of intention*

A questionnaire will use validated, standardized item stems to measure intentions, attitudes, norms, and self-efficacy regarding use of TeachTown online and offline (separately). The stems for each question were designed to be adapted for study of any behavior and have been used to successfully predict a large variety of behaviors [54–59].

*Teachers’ intentions* to use TeachTown online and offline components for instruction of students with ASD will be measured by two items (e.g., “How likely is it that you will use TeachTown for online instruction of students with ASD?”). Scaled response options will range from 1 (very unlikely) to 7 (very likely). If highly correlated, the two measures of intention will be aggregated for each behavior.

*Teachers’ attitudes,* or the extent to which one “likes” or “dislikes” using TeachTown components, will be measured by six (7-point) bipolar adjective scales, scored −3 to +3. For example, scales will allow respondents to rate using a TeachTown component as extremely unpleasant–extremely pleasant and as extremely wise–extremely foolish. The mean score across the six items will constitute our measure of attitudes toward using a TeachTown component.

*Teachers’ perceived norms* will be measured using two standard measures that capture perceptions of normative pressure. For example, respondents will be asked to rate on a 7-point scale the perception that most autism support teachers will use TeachTown online. If highly correlated, the two measures will be aggregated.

*Teachers’ self efficacy* will be measured by asking respondents to rate, on a 7-point scale, the statement, “If I really wanted to, I could use TeachTown online in my classroom” as likely/unlikely.

*Other covariates of interest* include years of teaching experience (measured through self-report) and staff-to-child ratios in the classroom (measured through direct observation).

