#### Quantitative approach

To examine changes in the use of EBP as a result of TeachTown, we will compare the use of EBP in the TeachTown group and control group in year 1. To address the questions of (1) whether increased use of TeachTown results in changes in the use of EBP, (2) TeachTown implementation changes intentions to use other EBP, and (3) whether TeachTown moderates the association between intentions and use of EBPs, we use data from year 1 for the intervention group and year 2 for the waitlist control, so measures will be from the first year that each classroom implements TeachTown.

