#### *Data collection*

Implementation climate and IT infrastructure will be measured at the beginning of each year. Measures of teachers’ intentions, attitudes, perceived norms, and self-efficacy regarding the use of the existing evidence-based practices will be measured in September and April of year 1 for the intervention group and year 2 for the control group. Surveys will be collected directly from the teacher.

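### Aim 3 asks whether TeachTown changes teachers' intentions to use EBPs, but its non-randomized analysis names only the time 2 intention and gives the September intention no stated role

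*Protocol article*

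**What the plan says.** All references are to the protocol article.

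- **The question.** Aim 3, Quantitative approach, lists as its second question whether "TeachTown implementation changes intentions to use other EBP". For this question "we use data from year 1 for the intervention group and year 2 for the waitlist control", which is the first year in which each classroom has TeachTown.
- **The data.** Aim 3, Data collection, states that intentions, attitudes, perceived norms and self-efficacy about the existing EBPs "will be measured in September and April of year 1 for the intervention group and year 2 for the control group".
- **The analysis.** Aim 3, Quantitative data analysis, describes analyses similar to those for EBP use, with "intentions to use each of the EBPs at time 2 as the outcomes of interest". It then sets a condition for going further: "If intentions are determined to vary as a function of TeachTown use", the effects of TeachTown on the determinants of intention are explored.
- **Covariates.** Aim 3 refers back to aim 2 for its methods. The other covariates of interest named there "include years of teaching experience (measured through self-report) and staff-to-child ratios in the classroom". An earlier EBP intention is not among them.
- **Timing elsewhere.** Table 1 lists the intentions and attitudes scale, under aim 2, as "Mid-year years 1 and 2".

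**The concern.** The question is about change, but the named outcome is a level at one time. In a randomized comparison, leaving out the earlier value would mainly cost precision. This comparison is not randomized. All classrooms in it have TeachTown, control teachers are due to be surveyed on EBP intentions only in year 2, and the exposure is how much each teacher uses the program. Randomization therefore does nothing to balance September intentions between heavy and light users.

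A teacher who is less inclined towards EBPs in September might use TeachTown more and still report low intention in April. The opposite pattern is equally possible. Either would produce an association between use and time 2 intention without any teacher's intention having changed.

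At stake is the reading of one part of the exnovation aim. An earlier difference between teachers could be reported as TeachTown eroding or supporting EBP intentions. It could also open the conditional second step on attitudes, norms and self-efficacy. The test is repeated for each of five EBPs.

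**Working it through.** **No plan figure to reproduce.** The article states no power, effect size or correlation for the intention analysis. Its teacher-level figure (80% power at d = 0.7) is for an intervention effect, a different contrast, and is not used here.

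**Inputs from the article.** Number of teachers: 35 + 34 = 69. Test: two-sided, alpha 0.05.

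**Inputs assumed.** The correlation of September intention with later TeachTown use, *r*, is taken from 0 to 0.5 in absolute value. The correlation of September with time 2 intention, *rho*, is taken from 0.4 to 0.8. TeachTown is given no effect, and use is related to time 2 intention only through September intention.

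**Step 1: spurious correlation.** Under these assumptions, the correlation of use with time 2 intention is *rho* × *r*.

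- *r* = 0.3, *rho* = 0.6: 0.3 × 0.6 = 0.18.
- *r* = 0.2, *rho* = 0.5: 0.2 × 0.5 = 0.10.
- *r* = 0: 0, whatever *rho* is.

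The sign of *r* sets the direction of the error but not its frequency in a two-sided test.

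**Step 2: how often this is significant.** Fisher's z has standard error 1/sqrt(69 − 3) = 1/sqrt(66).

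- 0.18: atanh(0.18) × sqrt(66) = 0.182 × 8.12 = 1.48. The chance of exceeding 1.96 in absolute value is about 0.32.
- 0.10: atanh(0.10) × sqrt(66) = 0.100 × 8.12 = 0.82, giving about 0.13.
- 0: 0.05.

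**Step 3: check by simulation.** This used 20,000 replicates of 69 teachers with no true effect. The rejection rate without the September value was:

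| *rho* | *r* = 0 | *r* = 0.2 | *r* = 0.3 | *r* = 0.5 |
|---|---|---|---|---|
| 0.4 | 5.1% | 9.6% | 16.2% | 38.1% |
| 0.6 | 5.0% | 17.1% | 32.1% | 72.1% |
| 0.8 | 5.0% | 26.0% | 51.8% | 93.7% |

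The middle cell (0.3 and 0.6) agrees with step 2. With the September value as a covariate, the rate was 4.7% to 5.1% in every cell. That return to 5% follows from the assumption that all confounding passes through the September score.

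**Step 4: is the September value a clean baseline?** Three places bear on this and do not settle it.

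- Teacher training in TeachTown puts the two-day training at the start of the school year.
- Aim 2, Data collection, places its intention survey straight after that training.
- Aim 3, Independent variables, says EBP intentions are measured as in aim 2.

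The September survey may therefore come before or after the training. Separately, reading time 2 as April rests on Aim 3, Data collection, while Table 1 gives a mid-year time for the intentions scale.

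**The case against.** The strongest reply is that the article is silent and does not exclude anything. A model adjusted for September intention also has the time 2 value as its outcome, so the wording fits one. The article lists no covariates for this analysis, and a fuller analysis plan might. The teacher-level power statement assumes one unnamed covariate, which could be the September value. This stands in part. A reader might infer that the plan rules September intention out, and the text does not support that. What remains is that a question about change is answered by a named single-time outcome in a non-randomized contrast, with no stated use for a measurement collected for the same teachers in the same year.

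Second, the article's reasoning runs from TeachTown to EBPs: teachers may cut back on EBPs because they see TeachTown as a substitute. It does not say that low EBP intention drives TeachTown use, and it also offers a competing hypothesis in which EBP use rises. This stands. Neither the sign nor the size of the assumed correlation comes from the documents, so a reader should not take 32%, or the larger cells of the table, as this trial's error rate.

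Third, adjustment may be oversold. If the September survey follows training, adjusting for it could remove part of the effect of introducing TeachTown. Intention is a two-item measure, so measurement error would leave some confounding behind, as would other differences between heavy and light users. This also stands, and it limits what the adjusted coefficient can be called.

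Fourth, the stakes are modest. Effectiveness is the primary outcome, and the gated step is exploratory. Agreed.

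**Conclusion.** The point holds in a limited form. As written, the Aim 3 intention analysis relates self-chosen TeachTown use to a single later measurement and gives the earlier one no stated role. Where September intention is related to later use, the result can reflect that earlier difference, and the follow-on analysis of determinants can start from it.

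The size is unknown. Under the assumed correlations with 69 teachers, the false-positive rate per EBP is 5% when use is unrelated to September intention, about 13% at 0.2 and 0.5, and about 32% at 0.3 and 0.6. These are illustrations of sensitivity and not estimates for this trial.

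Two further inferences are not supported. One is that adjusting for September intention would isolate a causal effect of TeachTown: it removes only confounding through the measured September score, and that score may itself follow training. The other is that a two-group power calculation shows what the omission costs, since this analysis is not a two-group contrast.

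**What to change.** 1. In Aim 3, Quantitative data analysis, state that time 2 intention for each EBP is modelled with the same teacher's September intention for that EBP as a covariate. Say the same for attitudes, norms and self-efficacy in the follow-on analyses.
2. Define time 2, and reconcile the September and April schedule in Aim 3, Data collection, with the mid-year entry in Table 1.
3. State whether the September survey precedes the TeachTown training. If it does not, describe the coefficient as change after training.
4. Report the result as an association with TeachTown use, because other differences between heavy and light users remain.

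The cost is a few sentences and one degree of freedom per model among about 69 teachers. No new data are needed, since the September survey is already planned.

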### Qualitative approach: How do teachers view TeachTown and its effects on their use of EBP?

#### *Participants*

We will recruit 48 teachers. Our purposive sampling strategy is presented in Table 1 and ensures that we will reach saturation in each quadrant [66].

#### *Method*

Semi-structured interviews will be conducted with teachers at the end of years 1 and 2. These interviews provide textual data that can be analyzed for themes, patterns, and ultimately, grounded theory [67]. Standardized probes will be included in the interview guide so that consistency across interviews is maintained. Interviews will be conducted by RAs under the direction of experts in qualitative research. We also will examine if the decision to exnovate is a conscious process. Specifically, we will query teachers’ rationale for using TeachTown; how they view TeachTown in relation to the other EBPs (e.g., complement, replacement) and the utility and effectiveness of each. Interviews will be digitally recorded with the participants’ permission, professionally transcribed, and loaded into Nvivo 10.0 software for data management and analysis.

#### *Qualitative analysis*

Interviews will be analyzed using an integrated approach [45]. Transcripts will be analyzed in an iterative process based upon an integrated approach that incorporates both inductive and deductive features [68]. Through a close reading of eight transcripts, the investigators will develop a set of codes to apply to the data (i.e., inductive approach). A priori codes derived from the original research questions and previous literature will also be applied (i.e., deductive approach). A random subset of transcripts (20%) will be coded by two investigators, and inter-rater reliability will be expected to be at least 90% [69]. Each reviewer will produce memos including examples and commentary to reach consensus regarding newly derived, emergent themes that emerged from the codes [68]. Once the data are coded, codes will be summarized and examined for patterns to create a tentative theory about the data.

#### *Mixed methods analysis*

We will integrate the qualitative findings with quantitative measures of teacher fidelity and factors associated with fidelity. The design taxonomy is as follows: the structure is simultaneous (we will gather quantitative and qualitative data concurrently and weigh them equally: QUAN + QUAL); the function is complementarity (to elaborate upon the quantitative findings to understand the *process* of change teachers experience); and the process is connecting (having the qualitative data set build upon the quantitative data set) [70]. We will use mixed methods in two ways. First, we will use quantitative findings to identify patterns in the qualitative data. To do this, we will enter quantitative findings into Nvivo as attributes of each participant. Quantitative attributes will be used to categorize and compare important themes among subgroups. Then, as themes emerge from the interviews, we can use Nvivo to query whether the presence and quality of these themes differ among teachers with low, average, and high fidelity. Second, we can use the qualitative data to help interpret quantitative results, especially if there are counterintuitive findings.

#### *Statistical power for quantitative analyses*

The prior trial of TeachTown reports that students made gains in communication skills of a moderate effect [71]. Meta-analytic reviews of studies of other interventions for children with ASD report large intervention effects [4, 72–74]. Based on this literature, we conducted a power analysis to determine the effect sizes we could expect in our cluster randomized study of students nested within the 70 classrooms in the district. Using the Power and Precision software package [75], we calculate that for student outcomes we will have power of 80% to detect a moderate intervention effect of *d* = 0.43, assuming enrollment of four students per classroom, an intraclass correlation (ICC) of 0.2, and inclusion of one covariate in our regression model that explains 15% of the variation. For teacher outcomes, we will have 80% power to detect a larger effect of the intervention (*d* = .7) assuming a model with a single covariate (*r*
^2^ = .15). All models assume two tailed tests with alpha = 0.05.

Our secondary goal is to test the potential impact of moderating factors. With the proposed sample size, the study will have power of 80% to identify an effect size associated with moderators of *d* = 0.65 [71], a moderate-to-large effect. For teacher-level analyses, we are powered to test moderators with an effect size of *d* = 0.85, a large effect.

## Discussion

The present study contains several important innovations. First, it relies on a strong partnership between our research group and the School District of Philadelphia [76], a critical component of implementation research. Through this partnership, we have gained an in-depth understanding of the barriers and facilitators to EBP implementation, making this an ideal setting in which to examine the implementation of a new technology.

Second, despite the growing popularity of CAI, the proposed study represents the first large-scale effectiveness-implementation study of a specific CAI for children with autism. Third, our study is one of the first to combine psychological theories of behavior change with organizational theories to examine predictors of EBP implementation. This information will provide valuable insight into modifiable factors which may affect the implementation of new technologies and identify possible implementation targets.

Finally, our study would be the first prospective study to examine changes in the use of existing EBPs as new practices are implemented. As denoted by the call for more research on this topic [77], little is known about what happens to existing practices when new practices are introduced. We will systematically study how the process of exnovation [33] unfolds as a new technology is introduced by evaluating changes in teachers’ use of existing EBPs and understanding why, after the TeachTown program is introduced.

This study provides an important opportunity to systematically evaluate the effectiveness of a new intervention for students with autism, while providing valuable insights into strategies to support the implementation of existing practices in public schools.
